# LIST OF ABBREVIATIONS AND RELEVANT DEFINITIONS

| **AE** | Adverse Event |
| --- | --- |
| **AR** | Adverse Reaction |
| **ASA** | American Society of Anaesthesiologists scale |
| **BMI** | Body Mass Index (weight in (kilogram)/ squire length (meters)) |
| **CA** | Competent Authority |
| **CCMO** | Central Committee on Research Involving Human Subjects |
| **CS** | CryoSeal |
| **CV** | Curriculum Vitae |
| **EU** | European Union |
| **EudraCT** | European drug regulatory affairs Clinical Trials GCP Good Clinical Practice |
| **F/E** | Flexion and Extension (knee function measured with goniometer) |
| **GMP** | Good Manufacturing Practice |
| **IB** | Investigator’s Brochure |
| **IC** | Informed Consent |
| **IMP** | Investigational Medicinal Product |
| **IMPD** | Investigational Medicinal Product Dossier |
| **INR** | International Normalized Ration (prothrombin time) |
| **METC** | Medical research ethics committee (MREC) (METC=Medisch Ethische Toetsing Commissie) |
| **MRC** | Medical Research Council scale; muscle power grading scale from 0-5 |
| **NSAID** | Non-steroidal anti-inflammatory drugs |
| **OR** | Operation Room |
| **(S)AE** | (Serious) Adverse Event |
| **Sponsor** | The sponsor is the party that commissions the organisation or performance of the research, for example a pharmaceutical company, academic hospital, scientific organisation or investigator. A party that provides funding for a study but does not commission it is not regarded as the sponsor, but referred to as a subsidising party. |
| **SUSAR** | Suspected Unexpected Serious Adverse Reaction  **TKA** Total Knee Replacement |
| **VAS** | Visual Analogue Scale |
| **WBP** | Personal Data Protection Act (WBP=Wet Bescherming Persoonsgevens) |
| **WMO** | Medical Research Involving Human Subjects Act (WMO=Wet Medisch-Wetenschappelijk Onderzoek met Mensen) |

# SUMMARY

**Rationale:** Fibrin Sealant is known to have some potential benefits for intraoperative use, especially in the acceleration of the coagulation cascade. Most studies with fibrin glue are focussing on the reduction of allogeneic blood transfusion and the possibilities to reduce costs. Firstly, fibrin sealant was made from patients’ blood plasma but the logistic problems made introduction in general hard. Now Sanquin has produced a CryoSeal (fibrin sealant) made of single-donor plasma which can be used during surgery. This application is already used in cardiothoracic surgery.

**Objective:** Is the application of CryoSeal (CS) in primary total knee replacement surgery beneficial for the patient with respect to a faster track and improved postoperative rehabilitation. The beneficial effect may be due to quicker functional knee rehabilitation, by pain reduction, better mobilisation and improved quality of life during the early postoperative period.

**Study design:** Multicenter, randomised controlled trial stratified by clinic.

**Study population:** Patients aged above 18 years scheduled for primary total knee replacement (TKA) because of osteoarthritis or rheumatic arthritis, meeting all the inclusion criteria and none of the exclusion criteria, are eligible for inclusion in the study.

**Intervention:** The intervention is the application of CryoSeal during surgery according to the standardised manner. The control group will receive standard care.

**Main study parameters/endpoints:** Primary endpoint: Difference in extension knee function 2 and 6 weeks after surgery. Secondary endpoints: postoperative complications, Pain score, knee function Flexion/Extension, Barthel score (day 3); Outpatient department scores (2 weeks, 6 weeks and 3 months, 1 year): Complications, Pain knee function, KSS, KOOS, SF-12, IPQ-K and EQ5D. A pre- and postoperative hand strength measurement will be performed since this might be a predictor of outcome after TKA. (Taekema 2010). Where possible, an actual physical activity measurement will take place to objectively analyse pre- and post operative acitivity level. (Groot, de 2008)

**Nature and extent of the burden and risks associated with participation benefit and group relatedness:** Given the origin of the CryoSeal product, i.e. donor plasma and in the absence of added bovine or chemical fibrinolysis inhibitors, no toxicity is to be expected by applying CryoSeal produced by the CS-1 (machine) / CP-3 (disposable) system, which was confirmed by pre and clinical research.

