## 4.4 Sample size calculation

We performed a sample size calculation for our primary outcome which is pre- to postoperative difference in knee extension angle at two weeks after surgery. We expect to find a difference between study arms of 10 degrees, which we also feel is clinically relevant. We have little prior data to base our calculations on, but we expect a standard deviation of 35 degrees in our primary outcome. We conclude that we need 250 patients in each arm to be able to detect the stated difference at significance level 4.9% with 90% power.

We have made a slight adjustment to the usual significance level of 5% because we plan to perform an interim analysis when a total of 250 patients have been included. At this time we will decide if the trial should be terminated early for efficacy or futility. If the trial continues, we will use the available data to estimate the standard deviation of the primary outcome. Based on this estimate, we will re-compute the sample size that is needed to achieve 90% power to detect a 10 degree difference between the study arms at level 5%. We will adjust the sample size accordingly. However, we will not include less than 400 patients or more than 600 patients.

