# 6. METHODS

## Study parameters and endpoints

Hypothesis

The hypothesis is that the application of CryoSeal (CS) during total knee replacement surgery is beneficial for the patient with respect to a faster track and improved postoperative rehabilitation. The beneficial effect may be due to quicker rehabilitation, by pain reduction, better mobilisation and quality of life (especially short time).

Primary endpoints

- postoperative knee function in extension difference as compared with preoperative extension function with goniometric at 2 and 6 weeks (in relation to secondary endpoints)

Secondary endpoints

- Grade flexion and extension difference after surgery
- Drain use or not
- Postoperative Hb/Ht
- Number of transfusions after surgery (according to appendix 1)
- Pain score
- Complications
- Total hospital stay and duration of rehabilitation
- Illness perception IPQ-K score
- Function improvement score (KSS, Barthel Index score, KOOS etc. see flowchart)
- Hand grip strength (measured with (Jamar) hand dynamometer)
- Activity Monitor

Study parameters

- Demographic data; gender, birth date (age), weight, length (BMI)
- Medical History; underlying diseases and home medication (including use of antibiotics prophylaxis and NSAIDs)
- Laboratory analysis; haemoglobin, haematocrit and blood view, CRP and erythrocyte sedimentation rate
- Operation details; anaesthesia, start- and end time of surgery, surgeon, type and time point placing and opening of drain, use of heparin, information about application of CryoSeal (if applicable), knee function after implantation of the implants
- Clinical data; number of transfusions (red cells, platelets and plasma), complications, removing drain, amount collected in drain, medication (including use of antibiotics and NSAIDs), discharge date
- Pain (score) at 24h post operative, and at 8:00 h each day until discharge from hospital.
- Rehabilitation; knee function during the first postoperative days, Barthel Index score and standard knee function scores (see Table 1).

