# 8. STATISTICAL ANALYSIS

Data will be analysed by the intention-to-treat principle. Demographic characteristics, variables from laboratory analysis and quantitative variables obtained from the clinical evaluation (Pain score, opioids consumption) will be reported as means, medians or percentages together with their standard deviations, as appropriate.

We will perform the following analysis of the primary endpoint. In all patients we test for a difference in mean pre- and post-operative extension angles between those with and without Cryoseal. Adjusting for pre-operative extension angles by analysis of covariance, we perform a two-sided test at level 0.049. In a secondary analysis, Fisher’s exact test will be used to determine the effect of use of fibrin sealant on adverse events. We will investigate whether the Cryoseal effect is modified by the use of a drain by adding drain use and the interaction between drain use and Cryoseal to the above analysis of covariance model. Also, effects within various other patients groups will be studied (e.g. gender, age, adipositas and rheumatic disorders)

Interim analysis and stopping rule:

We plan to perform a single interim analysis when a total of 250 patients have been included. At this time we will decide if the trial should be terminated early for efficacy. In all patients we test for a difference in mean pre- and post-operative extension angles between those with and without Cryoseal. Adjusting for pre-operative extension angles, we perform a two-sided test at level 0.005. If we are able to reject the null hypothesis, we terminate the trial and conclude efficacy of the treatment.

If the stopping rule is not met and the trial continues, we must set the level of significance of the final analysis to 0.049 to account for the fact that we performed an interim analysis. This is referred to as the O'Brien-Fleming rule.

Also, if the trial continues, we will use the available data to estimate the standard deviation of the primary outcome. Based on this estimate, we will re-compute the sample size that is needed to achieve 90% power to detect a 10 degree difference between the study arms at level 5%. We will adjust the sample size accordingly. However, we will not include less than 400 patients or more than 600 patients.

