**Analysis plan**

The study database will be closed and subsequently be de-blinded more than six weeks after the last surgery procedure of the FIRST-patients. This analysis plan will be registered at the Dutch trial register (NTR) and the ethics committee will be informed about protocol 4.1 before execution of the plan using the data from the closed database. The primary analysis will be performed as stated in the protocol. Subsequently, a for three variables stratified subgroup analyses of the primary end points will be performed. This will be folllowed by a pre-specified subgroup analyses using 19 variables for hypothesis screening.

Statistical analyses

In SPSS, for each subgroup the odds ratio (OR under randomized controlled conditions) or relative risk (by univariate- and multivariate analysis (MVA)) with the corresponding 95% confidence interval (CI) will be estimated for CryoSeal. Although subgroups of the study population are predominately formed based on confounding factors, we will investigate the stability of the effect estimates over different levels of the confounding factors by correction in the MVA for those confounders. When a preoperative variable is significantly associated with CrySeal use we will address this observation, however we continue the primary and secondary analysis using the pre-specified subgroups.

Confounding and effect modification

Normally the problem of confounding by indication is virtually absent in the study of side effects of medical interventions. In case of CryoSeal use however, the subgroup analyses does not correct for the possibility of effect modification. Effect modification could arise since patients when for example wound drains were placed and could change the susceptibility of the patients for effects by CryoSeal.

Interpretation of pre-specified subgroup analyses and “multiple testing”

The stratified subgroup analyses will be made with each pre-specified subgroups. There will be no correction for multiple testing because all subgroups are defined by variables which are known to have underlying associations with the primary endpoints of the study. All subgroups were specified before the data are available. The implications of the outcomes will be discussed in relation to all other associated estimates observe in all subgroups.

The Plan of pre-specified subgroup analyses

Subgroup analyses:

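### The primary ANCOVA adjusts only for pre-operative extension, although other baseline variables that the plan treats as prognostic are already collected: a valid test with a cheap, modest gain in precision left unused

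*Combined protocol and SAP*

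**What the plan says.** Section 8 (Statistical analysis) defines the final primary test: "Adjusting for pre-operative extension angles by analysis of covariance, we perform a two-sided test at level 0.049". The interim test adjusts for the same single variable: "we perform a two-sided test at level 0.005". No other covariate is named for either look. Drain use enters only in a separate interaction model. The addendum keeps the primary analysis as the protocol has it, and its multivariate models serve the subgroup estimates.

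Elsewhere the plan collects, and attaches prognostic meaning to, further baseline variables:

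- The Summary says of hand strength: "A pre- and postoperative hand strength measurement will be performed since this might be a predictor of outcome after TKA". The flow chart in section 3 places it at baseline, before randomisation.
- Section 6 (Study parameters and endpoints) records "Demographic data; gender, birth date (age), weight, length (BMI", together with medical history and home medication, NSAIDs included.
- The addendum justifies the absence of a multiplicity correction by saying that "all subgroups are defined by variables which are known to have underlying associations with the primary endpoints of the study". Its lists include age, sex, NSAID use and prednisone use.
- Section 8 names gender, age, adipositas and rheumatic disorders as patient groups to be studied, without claiming an association.

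**The concern.** The plan relies on prognostic value to justify uncorrected subgroup testing, but does not use it in the primary comparison, where it would help. If age, sex, NSAID use, prednisone use and grip do explain part of the variation in extension beyond the pre-operative angle, the residual variance of the primary test is larger than it needs to be. The treatment effect is then estimated with a wider interval, and power at a given sample size is lower at both looks. Adjustment for baseline predictors is sound only if the list is fixed before the data are unblinded, so the time to settle it is now.

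**Working it through.** **Inputs.** From section 4.4: difference 10 degrees, SD 35 degrees, and "we need 250 patients in each arm to be able to detect the stated difference at significance level 4.9% with 90% power". From section 8: final level 0.049 and interim level 0.005, both two-sided, with the interim at 250 patients (125 per arm). The R-squared of the added covariates, meaning the share of variance left after pre-operative extension, is not in the documents. It is an assumption, shown as a range.

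**Step 1: the plan's own figure.** n per arm = 2 × [35 × (1.9686 + 1.2816) / 10]² = 258.8, so 259, against the stated 250. Conversely, at 250 per arm SE = 35 × √(2/250) = 3.130, and power = Φ(10/3.130 − 1.9686) = Φ(1.226) = 89.0%. The stated 250 is a slight rounding down of the usual two-sided formula. That is a separate matter and neither helps nor harms this point.

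**Step 2: adding covariates.** Take 35 as the residual SD of the planned one-covariate model. Then SE = 3.130 × √(1 − R²), power = Φ(10/SE − 1.9686), and the equivalent n per arm under the present model = 250/(1 − R²).

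| R² of added covariates | SE | Power, 250 per arm | Equivalent n per arm | Total N for 90% |
|---|---|---|---|---|
| 0 | 3.130 | 89.0% | 250 | 518 |
| 0.02 | 3.099 | 89.6% | 255 | 508 |
| 0.05 | 3.051 | 90.5% | 263 | 492 |
| 0.10 | 2.970 | 91.9% | 278 | 466 |
| 0.15 | 2.886 | 93.3% | 294 | 440 |

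The R² at which 250 per arm reaches 90% is 1 − 250/258.8 = 0.034.

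**Step 3: interim look.** SE = 35 × √(2/125) × √(1 − R²) and power = Φ(10/SE − 2.807). This gives 29.2% at R² = 0, and 31.2%, 33.5% and 36.1% at 0.05, 0.10 and 0.15.

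**Step 4: cost if the covariates explain nothing.** Five added covariates use 5 of about 500 degrees of freedom, which inflates the variance of the treatment effect by roughly 5/500 = 1%. Then SE = 3.130 × √1.01 = 3.146 and power is 88.7%, a loss of 0.3 points. The break-even R² is therefore about 0.01. The table does not deduct this cost. With it, R² = 0.02 gives about 89.3% and R² = 0.05 about 90.2%.

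**Step 5: which variables qualify.** The addendum's statement covers all of its subgroup variables, but transfusion, hospital stay, surgery time, drain salvage and reinfusion, and peroperative Hb arise during or after surgery. They may be affected by treatment and cannot be covariates. Age, sex, home NSAID use and prednisone use can be known before randomisation. Section 6 also records NSAIDs during the hospital stay, and those values do not qualify.

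**The case against.** **The evidence of prognostic value is thin.** The addendum's statement is a one-line defence of uncorrected subgroup testing and covers variables that are not baseline at all. The same addendum calls those analyses exploratory and asks, as open questions, whether pre-operative NSAID and prednisone use correlate with the outcomes. Hand grip is said only to be a possible predictor of outcome after knee replacement in general, not of extension at 2 or 6 weeks. It is also a secondary endpoint, so it has another purpose. All of this stands, and it is why the size of the gain cannot be derived from the documents.

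**The main predictor is probably already in the model.** Only variance beyond pre-operative extension counts. Section 4.4 describes 35 degrees as the SD of the pre-to-post difference, not as an ANCOVA residual SD, so the 89.0% starting point gives no credit for the adjustment already planned. This also stands. The figures show relative gain, not the trial's true power.

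**Sample-size re-estimation protects final power.** Sections 4.4 and 8 recompute N from the observed SD to target 90%, within 400 to 600 patients. Within those limits poor precision would be paid for in patients rather than in power. That changes the form of the loss but does not remove it. If re-estimation uses the raw outcome SD, added covariates would not alter N, so the SD to be used must be named.

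**A stronger reading that the text does not support.** The addendum says "When a preoperative variable is significantly associated with CrySeal use we will address this observation", and a reader might infer that covariates will be chosen by chance imbalance after unblinding. The sentence goes on to say that the primary and secondary analyses continue with the pre-specified subgroups. It provides for a remark on the imbalance; no rule there puts a variable into the primary model. Nothing in it needs deleting on this account.

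**Conclusion.** The point holds as one of efficiency and pre-specification. The planned ANCOVA is valid, is specified in advance and adjusts for the outcome's own baseline. A reader should not infer bias or an inflated error rate from the short covariate list.

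On the plan's own premise, a small fixed set of baseline variables already being collected would reduce the residual variance. The assumed range of 2% to 15% corresponds to 0.6 to 4.3 power points at 250 per arm (89.6 − 89.0 and 93.3 − 89.0), before a cost of about 0.3 points. At the bottom of that range the gain is negligible. At an R² of about 0.034, or a little more once that cost is counted, it closes the gap to the stated 90%. These figures rest on the assumed R², on 35 degrees as the residual SD, and on complete data in 250 patients per arm. The case for the change is the asymmetry: a loss of about 0.3 points if the covariates are useless, against a larger possible gain.

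**What to change.** Before de-blinding, amend section 8 and refer to it in the addendum:

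- Primary model: post-operative extension on arm, pre-operative extension, age, sex, pre-operative NSAID use, pre-operative prednisone use and pre-operative hand grip. BMI and diagnosis (osteoarthritis or rheumatic arthritis) are optional, since section 8 names them only as subgroups.
- Use pre-randomisation values only. Transfusion, hospital stay, surgery time, drain salvage and reinfusion, and peroperative Hb stay out.
- Replace a missing baseline covariate by its overall mean, so that no patient is dropped.
- State that any sample-size re-estimation uses the residual SD of this same model.
- Keep the one-covariate model as a sensitivity analysis.
- Apply the list at the interim only if that analysis has not yet been run; otherwise to the final test alone.

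Clinic, the stratification factor, is a separate point, but it should also appear in the final formula.

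The cost is wording. No new data are needed; the price is about five degrees of freedom and a list that cannot be changed afterwards.

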# 1. INTRODUCTION AND RATIONALE

Fibrin Sealant, also referred to as “fibrin glue” consists of two components, one component is thrombin and the other one is cryoprecipitate with fibrinogen. When both components are combined the last step of the coagulation cascade is started; the conversion of fibrinogen in fibrin. CryoSeal can be used at the end of the operation to seal the bare bony surfaces (i.e. bone surfaces not covered by the prosthesis), and synovial tissue with the aim to decrease or prevent large postoperative bleeding at the surgical field. The patient’s coagulation system is also capable to stop excessive bleeding, but this will probably take longer. CryoSeal only fastens this process because of the higher amount of growth factors; it imitates the last phase of the coagulation process. [Spotnitz, Am J Surg 2000]

Fibrin sealant finds its application in open cardiac surgery, hip- and knee surgery, liver surgery and plastic surgery.

Working mechanism

Haemostasis is achieved when there is a good balance between coagulation, the complement of this and the conversion of fibrinogen in fibrin under influence of thrombin. This coagulation cascade is known with the complex interaction of plasma proteins, blood cells, blood flow and viscosity and endothelia of the blood vessels.

After tissue damage, platelets are activated and stick to the blood vessel, changes of the vascular tone and aggregation is started. After activation platelets produce thromboxane A2, inositol-3-phosphate and diacylglycerol, who further regulate the activation of platelets and the release of Ca2+. Ca2+ is an important co-factor in the different coagulation stages.

Furthermore the outer membrane of the platelets is transformed and in this manner creating a good surface for coagulation, the production of thrombin and in lengthening prolonged the production of fibrin. [Mackie, biology of haemostasis and thrombosis, 1996]

The several investigations with the application of fibrin sealant or platelet rich plasma show contradictions in outcome. Levy et al. found positive results of fibrin sealant in the amount of blood loss during and after surgery in total knee replacements. [Levy, JBJS-Am 1999] The conflicting results are caused by the product that’s used outcome variables and study design. At the moment it is possible to make fibrin sealant as an autologous component out of patient’s blood plasma or as a single-donor product produced by the blood bank.

The advantage of autologous fibrin sealant is that the patient does not receive donor blood and that fibrinolysis reducers are not necessary. Disadvantages are mostly of logistic and economic nature. The general condition of the patient must be adequate; furthermore the blood is not always used. Most of all GMP circumstances are difficult to realise at the OR.

Everts et al. compared the different manufacturing options of platelet gel and concluded that the platelet amount can be increased five fold in comparison with whole blood. But the quality of the end product is strongly dependent on the basic product. [Everts, Growth Factors 2006]

Sanquin has started the production of fibrin glue, CryoSeal (CS), of allogene single donor plasma as alternative. The production is equal as autologous fibrin glue. Only the plasma that is used for the production is quarantine plasma that is Parvo B19-safe. The production is performed under regulated circumstances which are GMP proved. The CS is saved deep freeze and is always available, only has to be thaw.

CS is currently under study on reducing transfusion needs during coronary artery bypass surgery in 4 Dutch Thorax centres, the so called FIBER study. In this prospective randomised multi-centre trial of approximately 1500 patients the primary endpoints are amount of allogeneic blood transfusions and the duration of intensive care stay. The results are not yet available but the pilot study showed no side effects or CryoSeal related complications.

This study proposal may provide evidence based support for improved postoperative rehabilitation by using CS after total knee surgery and will contribute to optimal blood product management in orthopaedic surgery patients. The mechanism for this improved rehabilitation may by through reduction of the intra-articular bleeding, resulting in subsequent reducing postoperative pain and facilitating earlier postoperative functional improvement i.e. faster gain of knee flexion and knee extension. Sanquin’s centre for clinical research located at the Blood Bank Region Southwest approves designs and coordinates randomised controlled trials (RCT) together with principle investigators. Initiated from this collaboration, this project is a continuation of previously completed clinical research projects (TOMaat, Trigger & Drain studies) with the department of orthopaedic surgery of the LUMC (head: prof.dr. [name]) and Sanquin researchers. The main objective of these studies was to define optimal transfusion management in orthopaedic surgery: Transfusie op Maat: ‘TOMaat study’. The infrastructure of the TOMaat trial can be used for the current question; on the clinical effectiveness, postoperative pain and early knee function of CS use in knee surgery.

